### Statistical analysis

Intention-to-treat analysis and analysis per protocol will be carried out according to CONSORT recommendations [127]. The three groups at baseline will be compared to verify that there are no significant differences between them and, therefore, to confirm that they are comparable after randomization. One-way ANOVAs will be used for continuous variables and Chi-square tests of independence for categorical variables. For continuous outcome measures in the post-test, the assumption of homoscedasticity will be evaluated with the Levene test. If this assumption is met, the usual F-test will be applied for all three groups to compare post-test means. When the assumption of homoscedasticity is not met, Brown-Forsythe F test will be applied. Statistically significant F-tests will be followed by post hoc comparisons. In addition, Tukey procedure, will be applied when the assumption of homoscedasticity is met, and the Games-Howell procedure if it is not.

The intention-to-treat principle will be used to analyse primary and secondary post-treatment outcomes and at 3-month follow-up, using mixed-effect models with a maximum likelihood estimate of complete information, to properly evaluate data missing from repeated ANOVA measurements [128]. The results of the ANOVA and post-hoc comparisons were supplemented by calculating effect sizes using Cohen’s standardized mean difference [90]. The effect sizes will be calculated to compare both changes within a group and between groups, all based on a combined standard deviation. Per protocol analysis (completers) will be carried out to help draw conclusions about maximum treatment efficacy [129].

When the trial is completed, the analytical methodology of the RCT will be reviewed to select the most appropriate analytical procedures prior to data analysis.

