## Methods/design

### Study design

A three-armed, single blind, randomized controlled trial (RCT) with repeated measurements at three times (at baseline, 6 weeks, and 3 months follow up) will be conducted in four Spanish-speaking countries (Spain, Argentina, Colombia, and Mexico). Due to the nature of the study, the condition will be notified to participants of to which they have been assigned, but those allocated to the intervention groups will remain unaware of the type of intervention they will receive. Participants who meet the inclusion criteria will be randomized to one of the three study arms in a 1:1:1 ratio: 1) unguided internet-based resilience intervention (CORE); 2) unguided healthy lifestyle program (HLP); and 3) Waiting list control (WL). Participants allocated to the WL condition will receive access to the intervention once they have completed the evaluation period.

The study has been approved by the Ethics Committee of University Jaume I in Spain, it was registered with the trial code NCT03903978, and it will be conducted in accordance with the CONSORT 2010 statement [86, 87], the CONSORT-EHEALTH guidelines [88], and the SPIRIT guidelines [89]. Figure 1 shows the study design.

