### Sample size calculation

The primary outcome is the change in the resilience levels from baseline to post-intervention. Therefore, the Connor-Davidson Resilience Scale (CD-RISC) scores will be compared before and after the intervention in the CORE, HTP, and WL groups to obtain information about the normality of the CD-RISC scores within the target population. So far, there are no data on the effect size obtained for Internet-based interventions to promote resilience. However, a recent meta-analysis [37] compared the effectiveness of psychotherapy as an outcome for improving resilience in mental health and psychological well-being, and the authors found a moderate positive effect of resilience interventions (0.44, 95% CI 0.23 to 0.64). Considering these findings, the sample size was calculated with a significance level of 0.05, for a potency of 0.80. We take a conservative approach, we assume an effect of 0.5 (Hedges’ g), which, according to Cohen [90], can be considered a medium magnitude effect. Since our design included three experimental conditions (CORE, HLP, WL), one-way ANOVA was assumed for the statistical analyses. The total sample size calculated is 249 Estimating a potential dropout rate of 30%, the total sample size was determined to be 324, requiring 108 subjects in each condition [91].

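### Non-significant baseline tests are taken as confirmation that the arms are comparable, an inference these tests cannot support

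*Protocol article*

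**What the plan says.** Participants are "randomized to one of the three study arms in a 1:1:1 ratio". The Statistical analysis section then plans a check that randomisation produced similar groups: the arms "will be compared to verify that there are no significant differences between them and, therefore, to confirm that they are comparable after randomization". The tests are named: "One-way ANOVAs will be used for continuous variables and Chi-square tests of independence for categorical variables".

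The section gives no significance level for these tests, no list of variables, no margin for an acceptable imbalance, and no consequence if a test is significant. It goes on to compare post-test means across the three groups by an F-test (Brown-Forsythe if variances differ), naming no baseline covariate. For the intention-to-treat analysis it plans mixed-effect models with full-information maximum likelihood, without giving their terms. It closes by leaving the choice of analytical procedures open for review once the trial is complete.

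**The concern.** The word joining the two halves of the sentence makes non-significance the evidence for comparability. That fails in both directions.

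- **A significant test says little.** With properly randomised arms, any baseline difference is a chance difference, and a fixed share of tests will cross the threshold.
- **A non-significant test says little.** It sets no limit on the imbalance. A gap in T0 resilience can be too small for the test to flag and still carry into the comparison of post-test means.

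At stake is a published statement that the arms are comparable which the tests cannot support, next to a post-test comparison that, as described, does nothing about whatever imbalance is present.

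**Working it through.** **The plan's own figures.** The article states no error rate for the baseline tests, so there is none to reproduce. The arm size is explicit: "Estimating a potential dropout rate of 30%, the total sample size was determined to be 324, requiring 108 subjects in each condition" (249 × 1.3 = 323.7, rounded to 324; 324 / 3 = 108).

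**Inputs**
- n = 108 per arm, three arms (Sample size calculation; Study design).
- Alpha 0.05 per test, uncorrected. This is an assumption: the article gives 0.05 only for the sample size ("the sample size was calculated with a significance level of 0.05, for a potency of 0.80").
- Variables available: 14 instruments marked at T0 in Table 4, 10 sociodemographic variables and 2 health-related ones (Other measures). That is 24, or 26 with the health items.

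**1. What observed gap can the F-test flag?** Let d be the observed gap between the extreme arms, in units of the within-arm SD. Then F = n × Σ(deviation²) / 2, where Σ(deviation²) is (2/3)d² if one arm is off and the other two coincide, and (1/2)d² if the third arm is midway. The critical value F(2, 321) at 0.05 is 3.02.
- One arm off: d = √(2 × 3.02 / (108 × 2/3)) = 0.29.
- Evenly spread: d = √(2 × 3.02 / (108 × 1/2)) = 0.33.

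For a given observed gap the result is fixed:

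| Observed gap | One arm off | Third arm midway |
|---|---|---|
| 0.25 SD | F = 2.25, p = 0.107 | F = 1.69, p = 0.19 |
| 0.30 SD | F = 3.24, p = 0.040 | F = 2.43, p = 0.090 |

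**2. How often do such gaps occur and pass?** I simulated three arm means under correct randomisation (400,000 draws).

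| Largest gap at least | Share of trials, per variable | Of these, non-significant |
|---|---|---|
| 0.20 SD | 31% | 84% |
| 0.25 SD | 16% | 69% |
| 0.30 SD | 7% | 32% |

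**3. How often would something be significant by chance?** For k independent tests the probability is 1 − 0.95^k: k = 14 gives 51%, k = 24 gives 71%, k = 26 gives 74%. With the 14 scales inter-correlated and the other variables independent (simulated, 2,000 runs each):

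| Tests | Correlation 0.3 | 0.5 | 0.7 |
|---|---|---|---|
| 14 scales + 12 others | 68% | 64% | 60% |
| 14 scales + 10 others | 67% | 61% | 55% |
| 14 scales only | 45% | 36% | 27% |

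**4. What does a passed gap do to the post-test contrast?** With a T0–T1 correlation r, an observed baseline gap d shifts the expected unadjusted post-test difference by r × d. The article gives no r. At assumed values of 0.5, 0.6 and 0.7, a gap of 0.25 SD shifts it by 0.125, 0.15 and 0.175 SD, which is 25 to 35% of the planned effect ("we assume an effect of 0.5").

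**5. Is type I error inflated?** Averaged over randomisations, the unadjusted pairwise test stays at 5%. Restricted to trials whose baseline F-test was non-significant, simulation at r = 0.5, 0.6 and 0.7 gives about 4.5, 4.3 and 4.1%.

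**The case against.** The strongest reply is that nothing depends on these tests. The section names no adjustment, exclusion or model choice triggered by a baseline p-value, and the intention-to-treat analysis uses mixed models on repeated measurements, of which baseline is one. The Sample size calculation section also describes the primary outcome as a change from baseline. Much of this stands: the sentence alone does not damage the trial, and a mixed model that accounts for baseline would deal with the imbalance. The article does not say that it does. That detail may properly sit in an analysis plan that is not shown. The post-test F-test is described here, however, and its description includes no baseline term.

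Three stronger readings are tempting and are not supported.

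- **The F-test misses important imbalances more than half the time.** Power calculations give miss rates such as 54% at 0.25 SD with one arm off, but they refer to a true population shift between arms, which randomisation rules out. For an observed gap the result is fixed, as step 1 shows. The article also defines no size at which imbalance matters.
- **False positives rise to between 11 and 17%.** Those rates apply only given an observed pairwise gap of exactly 0.25 SD, at r = 0.5 to 0.7. A gap at least that large occurs for a given pair in about 6.6% of correctly randomised trials, and the overall rate is 5%.
- **The plan would declare sound randomisation a failure about 60 to 70% of the time, and then adjust for whatever was significant.** This needs an alpha, a variable list and a rule that one significant test denies comparability. The article states none of them, nor any adjustment that would follow.

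**Conclusion.** The point holds as a fault of inference written into the plan: non-significance cannot confirm comparability. The size rests on 108 per arm and an assumed 0.05 per test. Gaps below about 0.29 SD are never flagged, and gaps from there to 0.33 SD are flagged or not according to where the third arm lies. About one correctly randomised trial in six has a gap of at least 0.25 SD on a given variable, and roughly seven in ten of those would pass. At least one chance significance would be expected in about 60 to 74% of trials if all 24 to 26 variables were tested (55% for 24 variables with scales correlated at 0.7), and in 27 to 51% if only the 14 scales were.

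The consequence is limited. Type I error is not inflated overall, and the trial is not invalidated. What remains is an assurance without support, and chance imbalance and imprecision that the post-test F-test could avoid. The mixed models avoid them only if they account for baseline. This is worth correcting before analysis.

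**What to change.** 1. Delete the baseline ANOVA and chi-square tests and the statement that they confirm comparability.
2. Summarise baseline by arm: mean and SD, or number and percentage, optionally with standardised differences. Let comparability rest on the randomisation procedure.
3. Adjust the post-test comparison for the T0 value of the outcome, by ANCOVA or by accounting for baseline in the mixed model. State that this is fixed in advance and applies whatever baseline differences are observed. If the analysis plan already says so, the article's description of the F-test should be brought into line with it.

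The cost is a few sentences of analysis wording. T0 values are already collected for the outcomes to be adjusted, so no new data or participants are needed. The only loss is a column of p-values in the baseline table. The gain is precision: adjustment leaves a residual variance of about 1 − r², which is 0.75, 0.64 and 0.51 of the unadjusted variance at assumed correlations of 0.5, 0.6 and 0.7.

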Online intervention is a growing field, given the increasing rates of access to technologies to people, the reducing on cost, and the potential advantages that this way of dispense the intervention provides (e.i. the scalability, overcoming geographical barriers, increasing in flexibility on time schedule …). Studies testing this kind of approach have been mainly conducting in developed countries with high or upper-middle incomes. Lately, efforts on testing the interventions in developing countries have been done. Protocols developed or validated on Western countries started to be adapted and tested [78–81] with different methodologies [82]. The evidence on the effects in countries with middle or low income are promising [79, 83, 84], but is still scarce [85]. One potential gap is the lack of resources to properly develop, adapt, and test the interventions. In this sense, the widespread use of Spanish language provides an opportunity to test already validated interventions in other countries with the need of minor changes. Therefore, the objective of the study is to test the effectiveness of an Internet-based preventive program to promote resilience and coping skills in college students at risk of developing emotional disorders in Spanish-speaking countries: Spain, Argentina, Colombia, and Mexico, compared to a healthy lifestyle program and a waiting list control group. The hypotheses are that the CORE program will improve the resilience, coping skills, and psychological well-being of college students. In addition, CORE and active control of Healthy Lifestyle are expected to be more effective than the Waiting List control group, but with greater and statistically significant effects of CORE as an intervention that is targeting to promote resilience.

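### The Tukey or Games-Howell step after a significant F-test is redundant with three arms and costs power for CORE versus HLP

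*Protocol article*

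**What the plan says.** The end of the Background section states pairwise hypotheses: "CORE and active control of Healthy Lifestyle are expected to be more effective than the Waiting List control group", with CORE expected to do better than HLP as well.

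The Statistical analysis section compares post-test means across the three arms with the usual F-test, or the Brown-Forsythe version if Levene's test rejects equal variances. Then: "Statistically significant F-tests will be followed by post hoc comparisons". The next sentence adds that the Tukey procedure "will be applied when the assumption of homoscedasticity is met, and the Games-Howell procedure if it is not". The natural reading is a gate followed by an adjusted pairwise procedure, although the linking words leave it slightly open whether Tukey is itself gated.

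The same section plans mixed-effect models for the intention-to-treat analysis of primary and secondary outcomes. It states neither a gate nor an adjustment for the contrasts from those models.

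On size, the Sample size calculation section says "the sample size was calculated with a significance level of 0.05, for a potency of 0.80", "we assume an effect of 0.5" (Hedges' g) and "one-way ANOVA was assumed for the statistical analyses". It continues: "The total sample size calculated is 249", and "Estimating a potential dropout rate of 30%, the total sample size was determined to be 324".

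**The concern.** The scientific question is pairwise. CORE versus HLP matters most, because it shows whether resilience training adds anything beyond another active programme. The plan as worded puts two layers of family-wise protection in front of that comparison. Each layer is sufficient alone when there are three arms and equal variances. If the second layer buys no error control, any power it removes is lost for nothing.

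**Working it through.** **Why the gate is enough with three arms.** The pairwise null hypotheses are CORE = HLP, CORE = WL and HLP = WL. If any two hold, so does the third, so every intersection of two or more of them is the global null. A closed test therefore needs only a 5% test of the global null (the F-test) and a 5% test of each pair. Rejecting a pair when both are significant keeps family-wise error at or below 5% under equal variances.

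**The plan's own figure.** The power of one two-sided pairwise test of 0.5 SD with the Tukey critical value is P(|T| > q/√2), where T is noncentral t with 3n − 3 degrees of freedom and noncentrality 0.5 × √(n/2).
- n = 82: power just under 0.800 (0.7998).
- n = 83: df = 246, q/√2 = 2.358, noncentrality 0.5 × √41.5 = 3.221, power 0.805. Total 3 × 83 = 249, as stated.

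The article does not name Tukey in the sizing. An omnibus F with f = 0.20 gives 246, so this shows consistency rather than the method used. The final figure is 249 × 1.3 = 323.7, rounded to 324.

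**Evaluable number.** 324 × 0.7 / 3 = 75.6, taken as 76 per arm.

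**Critical values at 76 per arm (225 df).** Tukey 2.359; unadjusted 1.971. With the same gate in front, the unadjusted rule rejects everything gated Tukey rejects, and more.

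**Simulation.** 300,000 replicates, normal data, SD 1 in each arm, two-sided 5% (the article does not state sidedness), 76 per arm. Power for CORE versus HLP:

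| Means CORE / HLP / WL | Tukey alone | Gate + Tukey | Gate + unadjusted |
|---|---|---|---|
| 0.5 / 0 / 0 | 0.765 | 0.762 | 0.836 |
| 0.75 / 0.25 / 0 | 0.765 | 0.765 | 0.865 |
| 0.5 / 0.25 / 0 | 0.210 | 0.209 | 0.327 |
| 0.75 / 0.5 / 0 | 0.207 | 0.207 | 0.332 |
| 0.25 / −0.25 / 0 (WL midway) | 0.764 | 0.752 | 0.779 |

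- Cost of the gate on top of Tukey (column 2 minus column 3): 0 to 0.3 points in the first four rows, 1.2 in the last.
- Gain from keeping the gate and dropping Tukey (column 4 minus column 3): 7.4, 10.0, 11.8, 12.5 and 2.7 points.

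**Error rates in the same simulation.**
- All arms equal, any false rejection: Tukey alone 0.050, gate + Tukey 0.045, gate + unadjusted 0.050.
- Only CORE differs (0.5 / 0 / 0), true null HLP = WL rejected: gate + Tukey 0.019, gate + unadjusted 0.050.
- Only WL differs (0.5 / 0.5 / 0), true null CORE = HLP rejected: 0.019 and 0.050.

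**Unequal variances.** Brown-Forsythe gate plus unadjusted Welch pairwise tests, 76 per arm, 200,000 replicates.
- One arm with SD 1.5 and the others 1: family-wise error 0.053 to 0.054 with all means equal; 0.045 to 0.050 for the remaining true null when one mean differs by 0.5.
- One arm with SD 2 and the others 1: family-wise error 0.058 to 0.059 with all means equal.

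Control is therefore approximate in this branch. The power of Games-Howell was not simulated.

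**The case against.** Tukey after ANOVA is conventional and valid. It supplies simultaneous intervals and adjusted p-values, and the stated 249 is what 80% power for one Tukey-adjusted difference of 0.5 requires. At 83 per arm, gate plus Tukey gives 79.5% to 80.5% for a CORE-HLP difference of 0.5. All of that stands: the plan contains no error here, and stacking the two layers does not by itself erode the planned power at 249. It does not rescue the adjustment, though. The plan already imposes the gate, and behind that gate a more powerful rule holds the same nominal error rate. At the 76 per arm left by the article's own dropout figure, gate plus Tukey gives about 0.75 to 0.77 for a 0.5 difference.

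A reader might infer a double penalty, with gate and adjustment each taking a share of the power for CORE versus HLP. The figures do not support that. Tukey alone and gate plus Tukey are almost identical for this comparison, and the gate costs about 1 point only when the waiting list lies between the programmes, contrary to the stated hypothesis.

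A reader might also infer that the hypotheses can be reached only through the F-test. The intention-to-treat mixed models carry no stated gate, so the text does not go that far. Detail on their contrasts may lie in a SAP that is not shown.

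Finally, the size of the gain depends on HLP effects that the article does not give. Where CORE-HLP is only 0.25 SD, power stays near 0.33 even after the change.

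**Conclusion.** The point holds as one of efficiency and wording. Once the 5% F gate is in place, the Tukey layer is unnecessary with three arms. At about 76 evaluable per arm, removing it adds roughly 7 to 13 percentage points of power for CORE versus HLP under the orderings the article hypothesises, and about 3 points if the waiting list lies midway. Family-wise error stays at about 5%.

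This rests on reading the two sentences as a gate followed by an adjusted procedure, two-sided tests, normal data, equal variances for the exact result, and assumed HLP-WL effects of 0 to 0.5 SD under the hypothesised orderings. The direction of the gain does not depend on the HLP effect; its size does. Under unequal variances, error control was 0.053 to 0.059 in the settings tried.

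**What to change.** For CD-RISC at the post-intervention assessment (T1), state one rule:

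1. Test arm overall at 5%, using Brown-Forsythe if variances differ.
2. If significant, test the three pairwise contrasts each at 5%, without Tukey or Games-Howell. Use Welch-type or heterogeneous-variance contrasts if variances differ.
3. Say that the same rule applies to the contrasts from the intention-to-treat mixed model.
4. Report all three differences with confidence intervals whatever the F-test shows.

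The article defers a review of its analytical methods until the trial is completed. This rule should be written down before then.

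The cost is analysis wording only; no extra recruitment or data are needed. The downsides are that the per-contrast intervals are not simultaneous and that family-wise control is approximate when variances differ. Tukey-type intervals can still be tabulated alongside for readers who want simultaneous coverage.

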Consequently, the strengths of this study focus on two aspects: First, to our knowledge, this would be the first RCT to evaluate an online intervention to improve the resilience of Spanish-speaking college students (in Spain and Latin America). Second, CORE is a three-armed, single blind multi-country (Spain, Argentina, Colombia, and Mexico) randomized controlled trial (RCT) that will make it possible to study the generalization of the results in different Spanish-speaking students. Third, we are comparing the results with an active control, a rigorous Healthy Lifestyle program developed in Spain and characterized by the promotion of habits of physical health, diet, and sleep, that although outcomes analyses are in progress, preliminary data show acceptance and effectiveness of this low-intensity internet program to reduce the symptoms of depression [93]. However, this study has some limitations: first, dropout rates are expected to be high, as reported in previous research [144, 145]. For this reason, dropout rates have been taken into account in the calculation of the sample size. Second, Internet-based interventions for mental health also raise some ethical issues with regard to the exchange of data between Europe and America. For this reason, international guidelines will be followed to address these concerns [146, 147], as well as all aspects of Personal Data Protection under existing European legislation in compliance with General Data Protection Regulation 2016/679.

We consider that this study will provide future lines of research that will strengthen the implementation of these interventions. Little is known about the potential for cultural adaptation and the efficacy of interventions for mental disorders in low- and middle-income countries [148]. According to World Bank data, Colombia and Mexico are considered upper-middle-income countries and Argentina is a high-income country. However, the WHO includes them in America region, where the prevalence of mental disorders is higher than in the European region, but this variation may be due to the fact that many people have both conditions (comorbidity) and to the relatively larger populations between these two regions [5]. These data suggest the importance of prioritizing the prevention and treatment of mental disorders globally in both developing and developed regions [6].

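### Effect sizes are worded as coming from the ANOVA and post hoc tests rather than the ITT mixed model, so baseline-related dropout could bias the between-group d in either direction

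*Protocol article*

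**What the plan says.** All of this is in the Protocol article.

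- **Statistical analysis, first paragraph:** post-test means of the three groups are compared by an F-test (Brown-Forsythe if variances differ), followed by Tukey or Games-Howell. No analysis set or missing-data rule is given for this test.
- **Statistical analysis, second paragraph:** ITT analyses of primary and secondary outcomes, post-treatment and at follow-up, use mixed models with full-information maximum likelihood, expressly to deal with missing data. The next sentence reads "The results of the ANOVA and post-hoc comparisons were supplemented by calculating effect sizes using" Cohen's standardised mean difference. Then: "The effect sizes will be calculated to compare both changes within a group and between groups, all based on a combined standard deviation". No effect size is tied by name to the mixed model. A completers analysis is listed separately as per protocol.
- **Sample size calculation:** the primary outcome is change in CD-RISC from baseline to post-intervention. On attrition: "Estimating a potential dropout rate of 30%, the total sample size was determined to be 324, requiring 108 subjects in each condition".
- **Discussion:** "dropout rates are expected to be high, as reported in previous research". No dropout by arm is given or predicted.

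**The concern.** The plan chooses a likelihood-based model because T1 scores will be missing, then attaches its effect sizes to an analysis that, on the most natural reading, ignores those missing scores and does not use baseline. If students who leave differ at baseline from those who stay, and do so differently by arm, the arms still observed at T1 are no longer balanced at T0. An unadjusted difference in post-test means carries that imbalance into d.

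Arm-specific dropout is plausible. CORE has six modules with homework, HLP has four modules, and the waiting list has none and receives CORE only after its last assessment.

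The standardised difference is also what later work is likely to reuse. This protocol took its own planning evidence from a pooled standardised effect of 0.44.

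**Working it through.** **1. The plan's own figures.** The inputs are: "the sample size was calculated with a significance level of 0.05, for a potency of 0.80"; "we assume an effect of 0.5 (Hedges’ g"); "one-way ANOVA was assumed for the statistical analyses"; "The total sample size calculated is 249". A Tukey-adjusted pairwise comparison of three arms at d = 0.5, alpha 0.05 and power 0.80 needs 83 per arm, and 3 × 83 = 249. Then 249 × 1.30 = 323.7, rounded to 324. At 30% dropout, 324 × 0.70 = 226.8 students remain, about 76 per arm. The protocol gives no figure for bias in d, so from here only d = 0.50 and the 30% come from the document.

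**2. Model (assumptions, not in the document).** T0 and T1 are standard normal within arm with correlation r, and the true CORE-minus-WL difference at T1 is 0.50 SD. Dropout follows logit P(drop) = a − b × T0, with a set to give the stated rate. Positive b means low scorers leave. Let m be the mean T0 of stayers in an arm. Then

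observed d = [0.50 + r × (m_CORE − m_WL)] / pooled SD of stayers at T1.

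**3. Two worked cases.**

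- 30% dropout in both arms, b = 0.5 in CORE and 0 in WL. CORE dropouts lie 0.48 SD below stayers at T0, so m_CORE = 0.143 and m_WL = 0. At r = 0.6: (0.50 + 0.6 × 0.143) / 0.996 = 0.588.
- 40% dropout in CORE and 20% in WL, high scorers leaving (b = −1 in both). m_CORE = −0.332 and m_WL = −0.173. At r = 0.7: (0.50 − 0.7 × 0.159) / 0.967 = 0.402.

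**4. Range (true d 0.50; numerical integration).**

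| Dropout CORE/WL | Who leaves | r = 0.3 | r = 0.5 | r = 0.7 |
|---|---|---|---|---|
| 40/20% | unrelated to T0 | 0.500 | 0.500 | 0.500 |
| 30/30% | low scorers, b = 0.5 in both | 0.501 | 0.503 | 0.506 |
| 30/30% | low scorers, b = 1 in both | 0.503 | 0.509 | 0.518 |
| 40/20% | low scorers, b = 0.5 in both | 0.529 | 0.549 | 0.571 |
| 40/20% | low scorers, b = 1 in both | 0.551 | 0.589 | 0.632 |
| 30/30% | low scorers, b = 0.5 in CORE only | 0.543 | 0.573 | 0.603 |
| 30/30% | low scorers, b = 1 in CORE only | 0.578 | 0.632 | 0.689 |
| 40/20% | high scorers, b = −0.5 in both | 0.473 | 0.456 | 0.440 |
| 40/20% | high scorers, b = −1 in both | 0.455 | 0.428 | 0.402 |

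These are illustrations, not bounds. Harsher combinations go further: 40/20% with b = 1 in CORE only gives 0.745 at r = 0.7, and 30/30% with b = −1 in CORE only gives 0.329.

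**5. The ITT model under the same mechanism.** Given T0, stayers and dropouts have the same T1 distribution, so the baseline-conditioned contrast is 0.50 in every row. Large-sample simulation of the maximum-likelihood estimate agrees to within 1%.

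**6. Where the ITT model also fails.** If dropout depends on the unobserved T1 score (40/20%, low scorers leaving, slope 0.5 to 1 in both arms, r from 0.4 to 0.7), the completer d is about 0.61 to 0.71 and the maximum-likelihood d is still 0.56 to 0.69.

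**7. Scale.** With 75.6 per arm, SE(d) ≈ √(2/75.6 + 0.50²/(4 × 75.6)) = 0.165. A bias of 0.10 is about 0.6 SE.

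**The case against.** The effect-size sentence has a second reading. It stands in the ITT paragraph, straight after a reference to repeated-measures ANOVA, and the next sentence promises within-group changes, which a one-way ANOVA of post-test means cannot supply. So at least some effect sizes must come from the repeated-measures data. The section never says that the ANOVA is limited to students with a T1 score, and it labels a completers analysis separately. This stands as a real ambiguity. It does not settle the source of the between-group d, because the mixed model is given no post hoc procedure and no effect size of its own.

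It can also be said that such detail belongs in a fuller analysis plan. But the article does not leave the source open. It names one, and not the one chosen for missing data.

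A reader might infer that the CORE effect will be overstated by about a fifth whenever dropout differs by arm. The document does not support that. Unequal dropout unrelated to score gives no bias, and the sign turns if high scorers leave. A fifth is one point in a range set by an assumed dropout pattern and correlation. Entry is restricted to students about 1 SD below the mean, which tends to lower r and shrink the bias: at r = 0.3, the milder CORE-only case gives 0.54.

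Nor does the document say that its principal p-value and its principal effect size come from different populations. It ranks neither the p-values nor the effect sizes.

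**Conclusion.** The point holds as a defect of wording with a possible effect on the result. The between-group d is tied, on the most natural reading, to observed and unadjusted post-test means, while the ITT model adopted for missing data carries no effect size. If dropout depends on baseline resilience to a different degree or at a different rate by arm, that d is biased: about 0.40 to 0.69 around a true 0.50 in the tabled scenarios. The bias is nil when dropout is unrelated to score and at most 0.02 when pattern and rate match across arms.

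The arm-specific rates, slopes and r are assumptions. The document fixes neither the size nor the direction. Moving to the ITT model removes the bias caused by baseline-dependent dropout, but only part of any bias caused by dropout that depends on the unseen T1 score.

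**What to change.** Replace the effect-size sentence with wording such as:

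> Between-group effect sizes at T1 and T2 are the arm contrasts from the ITT mixed model, which includes baseline CD-RISC, divided by the pooled baseline SD of all randomised students, with 95% confidence intervals. Any effect size computed from the ANOVA is labelled complete-case and is supplementary.

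For the other outcomes, the corresponding baseline score takes the place of CD-RISC. Because entry selects low scorers, the baseline SD may be narrower than the T1 SD. Name the SD beside each d and give the contrast in scale points as well.

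The cost is one sentence and a few lines of code, with no new data and no change to the sample size. The reported effect may be slightly less favourable.
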